# Effectiveness of sexual health influencers identified by an ensemble machine learning model in promoting secondary distribution of HIV self-testing among men who have sex with men in China: study protocol for a quasi-experimental trial

**DOI:** 10.1186/s12889-021-11817-2

**Published:** 2021-09-28

**Keywords:** Sexual health influencers, Ensemble machine learning, Secondary distribution, HIV self-testing, Men who have sex with men, China

## Abstract

**Background:**

HIV self-testing (HIVST), especially the secondary distribution of HIVST (SD-HIVST) initiated by sexual health influencers (SHIs), has been recognized as an effective strategy in promoting HIV testing, especially among men who have sex with men (MSM). This quasi-experimental study aimed to evaluate whether SHIs identified through the ensemble machine learning approach can distribute more HIVST than those who identified by the empiricalscale.

**Methods:**

We will recruit eligible adults (≥18 years old) who were assigned male gender at birth, and willing to participate in potential SD-HIVST online. Participants will be assigned randomly to two groups (scale group or machine learning group), followed by a separate process of SHI identification based on the group assignment. After identification, all index participants (defined as identified SHIs who are verbally consented to participate in SD-HIVST or who directly order HIVST kits) will follow the same procedure for SD-HIVST acquisition and distribution. Index participants can order HIVST online and distribute them to members within their social networks (defined as alters) in-person or virtually through a personalized peer referral link. Once a unique alter uploads a photographed test result to the platform, both the alter and the corresponding index participant will receive a fixed incentive of 3 USD. The index MSM can order up to five HIVST in the first three months and ten HIVST in the following three months. Each index participant will need to complete a baseline survey at the first-time ordering and one to two follow-upbased on the times of ordering,, three months after ordering. This trial will be comparing 1) the mean number of alters motivated by each index participant in each group and 2) the mean number of newly-tested alters motivated by each index participant in each group.

**Discussion:**

In promoting the efficacy of identifying SHIs for SD-HIVST, our study has the potential to enhance testing coverage, particularly among marginalized individuals and those who are reluctant to for HIV and other sexually transmitted infections.

**Trial registration:**

We registered the study on the Chinese Clinical Trial Registry website on 4th November 2021, with registration number ChiCTR2000039632.

## Background

The global human immunodeficiency virus (HIV) epidemic has been well controlled [1, 2]. However, study findings still reinforce the need for further attention to men who have sex with men (MSM) regarding HIV prevention. For instance, the HIV prevalence among MSM in China has increased from 0.5% in 2003 to 8.0% in 2015 and stays consistent afterward, while this also consistently stands highly of HIV incidence in China [3–5]. The lack of HIV status awareness is one of the main identified reasons for the high HIV infection rate among the MSM population [1]. Unfortunately, a recent statistic showed that more MSM in China (about 40–50%) than in other developed countries are less likely to have tested for HIV in the last 12 months [6]. Therefore, HIV testing is considered the key and the first step needed in HIV transmission prevention, specifically among MSM [7]. Following testing, the need for successful linkage to care and treatment for all diagnosed persons living with HIV is also quite essential.

Compared with healthcare facilities-based tests, HIV self-testing (HIVST) affords users greater convenience, autonomy, and privacy [8, 9]. HIVST is recognized globally as an innovative and reliable strategy to promote HIV testing. The World Health Organization (WHO) also recommends HIVST as an efficient testing approach for persons with low access to testing services and high-at-risk persons for routine testing [10]. Secondary distribution of HIVST kits (SD-HIVST) refers to a strategy where individuals (defined as index) obtain multiple HIVST kits and distribute them to members within their social networks (defined as alters) [11]. Currently, a growing number of empirical pieces of evidence have shown that SD-HIVST could contribute to the increasing coverage of HIV testing and effectively promote HIV case identification in diverse populations [12–14].

In addition, individuals within centralized networks could contribute to health behavior change among their peers [15] and increase the distribution of HIV self-testing kits [16] through SD-HIVST. How to effectively identify sexual health influencers (SHIs) among MSM is relevant in implementing SD-HIVST interventions. However, most preliminary studies employ self-reporting or empirical scales that cannot evaluate SHIs’ social network characteristics and have limited influence [17–21]. Therefore, we developed an ensemble machine learning model to help identify key SHIs [22]. This quasi-experimental trial sought to examine if SHIs identified through our trained ensemble machine learning model can facilitate more testing among persons who receive HIVST in the SD-HIVST intervention.

### Objectives

This trial aims to examine whether the SHIs identified by an ensemble machine learning model can motivate more alters to receive HIVST kits and more first-timers to test for HIV, compared to SHIs identified through an empirical scale.

### Hypothesis

We hypothesize that SHIs identified by the ensemble machine learning model will motivate more alters to test and identify more newly-tested alters (as first-time tested for HIV) through the SD-HIVST intervention than SHIs identified by the conventional scale.

### Trial design

This trial will be a double-blinded, quasi-experimental study with two parallel groups. The study duration is 12 months, from January 2021 to December 2021. We will randomly assign study participants into two groups in a 1:1 allocation ratio after recruitment. After that, we will use two distinct strategies (model-based and scale-based methods) in identifying the SHIs within each group who will receive the same intervention (SD-HIVST).

## Methods/design

### Study setting and recruitment

The study will be conducted jointly by the Social Entrepreneurship to Spur Health (SESH) team, Zhuhai Center for Diseases Control and Prevention (CDC), and Zhuhai Xutong Voluntary Services Center (Xutong), which is an MSM-friendly community-based organization (CBO).

We will post recruitment banner adverts on Blued, the largest online gay social networking application among MSM in China, in 5 provinces of southern China (Guangdong, Guangxi, Fujian, Hunan, Jiangxi). Interested MSM who click the banner posts will undergo an eligibility assessment using a set of pre-survey questions, and eligible participants will proceed to complete an online baseline survey.

### Eligibility criteria

To participate in the study, interested individuals are must meet the following criteria: 1) be assigned male gender at birth; 2) be at least 18 years or older; 3) self-report ever having sex with other men, and 4) be willing to participate in a potential secondary distribution of HIVST intervention.

### Interventions

We will randomly allocate eligible participants to either the scale group as controls or machine learning groupas the intervention group. A statistician will identify SHIs in the intervention group using an ensemble machine learning model and using a conventional scale for identification in the control group. All identified SHIs will be eligible to participate in the SD-HIVST intervention as index participants. We define index participants as those who were consented to participate in the program.

Index participants from both groups will follow the same study procedures for SD-HIVST with monetary incentives plus peer referral. They will be required to complete a survey at the beginning of the first-time ordering and one follow-up survey three months after each time they order HIVST kits. Figure 1 is the flowchart which shows the trial procedures.

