### Outcomes

Our first primary outcome is to compare the average number of alters motivated by each index between two groups. The second primary outcome is to ascertain the mean number of newly-tested alters motivated by each index in each group in the same study period. Secondary outcomes will be 1) the mean number of tested alters motivated by each index in each group with HIV reactive results, and 2) evaluate the primary outcomes in subgroups categorized by age, sexual orientation, sexual intercourse history, residence, and previous HIV testing experience.

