### Recruitment

The recruitment banner ads will have a brief trial description and continue showing on Blued until a target population size of at least 2000 eligible MSM participants fills in the baseline survey. Each Blued user will only be able to finish the baseline survey once. After survey submission, eligible study participants will receive a random 8-digit verification code and the WeChat ID of SESH. All participants will be encouraged to add the SESH official WeChat and provide their unique 8-digit verified code to get 25 RMB (≈ 4 USD) as the time reimbursement of survey completion. We will add participants who do not add the SESH WeChat or send them reminder text messages according to their provided contact information in the survey. After identification, we will use Wechat or text messages to notify SHIs and ask for their verbal consent to participate in the SD-HIVST.

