### Allocation and blinding

Study participants who are consented, meet inclusion criteria, and provide non-duplicate contact information (either cell-phone number or WeChat ID) will be randomly assigned to the scale group or the machine learning group by a computer-generated program with a 1:1 allocation. Only researchers will know the details of the group assignments, and study participants and CBO staff are blinded.

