#### Missing data plan

We will follow the intention-to-treat principle to conduct data analysis. Response to variables for primary and secondary outcomes analyses are required compulsory answers to complete the surveys. Therefore, we will not have any missing data in terms of analyzing the primary and secondary outcomes.

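### Both primary outcomes are averaged over SHIs who consent after randomisation, so identified SHIs who decline drop out of an analysis described as intention-to-treat

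*Protocol article*

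**What the plan says.** The order of events can be pieced together from several sections of the protocol article.

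- Randomisation comes first (Trial design): "We will randomly assign study participants into two groups in a 1:1 allocation ratio after recruitment".
- Identification comes next (Abstract, Methods): "followed by a separate process of SHI identification based on the group assignment". The section on the scale group intends the number selected there to match the number the model selects.
- Consent comes last (Recruitment): once SHIs are identified, "we will use Wechat or text messages to notify SHIs and ask for their verbal consent to participate in the SD-HIVST".

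The Interventions section defines the unit by that last step: "We define index participants as those who were consented to participate in the program". The Abstract words it differently: "all index participants (defined as identified SHIs who are verbally consented to participate in SD-HIVST or who directly order HIVST kits".

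The Outcomes section states: "Our first primary outcome is to compare the average number of alters motivated by each index between two groups". The second primary outcome, newly-tested alters, is also a mean per index. The Sample size section counts index participants: 400, or 200 per group. The Missing data plan states: "We will follow the intention-to-treat principle to conduct data analysis".

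**The concern.** The trial asks which identification method produces more tested alters. The Objectives and Hypothesis are framed in terms of SHIs identified by each method, not SHIs who go on to agree. Selecting SHIs after randomisation is the intervention itself, so restricting the analysis to identified SHIs is legitimate. The further restriction to those who consent is the problem. Consent is a response given after randomisation by men whom two different selectors have chosen, so the methods may differ in how many of their men agree.

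If they do differ, dividing by consenters rewards the method whose men agree less often but are more active when they do, even when both methods yield the same number of tests. The matching of numbers identified, which would have given a clean denominator, is lost at this step. Both primary outcomes are affected.

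**Working it through.** **The plan's own figure.** The stated 400 can be neither reproduced nor refuted, because no SD is given. With 20% loss, 200 × 0.80 = 160 evaluable per group. At two-sided 0.05 (sidedness assumed) and power 0.80, a difference of 1 alter implies SD = 1 / [(1.960 + 0.842) × √(2/160)] = 3.19. The point does not depend on this figure.

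**Size of the bias.** Let y be alters per identified SHI and c the consent rate. Decliners cannot order, so they contribute no alters and the per-index mean is y/c. The article gives neither y nor c; the values here are assumptions. With y = 0.9 in both arms (no true difference):

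| Consent, scale | Consent, model | Mean per index, scale | Mean per index, model | Model minus scale |
|---|---|---|---|---|
| 60% | 40% | 0.9/0.6 = 1.50 | 0.9/0.4 = 2.25 | +0.75 |
| 50% | 50% | 0.9/0.5 = 1.80 | 1.80 | 0 |
| 40% | 60% | 2.25 | 1.50 | -0.75 |

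Per identified SHI the difference is 0 in every row.

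**Imbalance needed to imitate the planned effects.** With equal total yield and a scale-group mean of m per index, a false +1 needs a model/scale consent ratio of m/(m + 1): 0.50, 0.67 or 0.75 for m = 1, 2 or 3. For the planned +0.3 newly-tested alters, with the article's 40% new testers applied to both arms, the ratio is 0.4m/(0.4m + 0.3): 0.57, 0.73 or 0.80.

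**Chance of a false claim.** Simulation with assumed inputs: 350 identified per arm, 1.0 alter per identified SHI in both arms, negative binomial counts with dispersion 0.5, Welch t-test, 4000 runs. The nominal rate of declaring the model superior is 2.5%.

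| Consent, model / scale | False difference per index | Model declared superior, per index | Model declared superior, per identified SHI |
|---|---|---|---|
| 60% / 60% | 0 | 2.4% | 2.8% |
| 55% / 65% | 0.28 | 16.6% | 2.1% |
| 50% / 70% | 0.57 | 52.6% | 2.2% |
| 40% / 70% | 1.07 | 88.6% | 1.8% |

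Exchanging the arms gives the same error against the model, by symmetry.

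**Power cost of counting decliners as zero.** Assume 50% consent in both arms, SD s = 3.16 among consenters, and means m of 1 and 2. The variance per identified SHI is c(s² + m²) − c²m².

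- Scale: 0.5 × (9.99 + 1) − 0.25 × 1 = 5.24.
- Model: 0.5 × (9.99 + 4) − 0.25 × 4 = 5.99.
- The difference in means falls from 1 to 0.5.
- 400 identified, 200 consenting per arm: z = 1/(3.16 × √(2/200)) = 3.16 per index; 0.5/√[(5.24 + 5.99)/400] = 2.98 per identified SHI.
- After 20% loss (320 and 160 per arm): z = 2.83 per index and 2.67 per identified SHI. Power is Φ(2.83 − 1.96) = 0.81 and Φ(2.67 − 1.96) = 0.76.

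**The case against.** Several points on the other side have force.

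- **Protections exist.** Eligibility requires willingness to take part in a possible secondary distribution, participants are blinded, and both arms follow the same procedure. These make unequal consent less likely. They cannot exclude it: willingness was stated before selection, consent is still asked afterwards, and the two methods may select different kinds of men.
- **The denominator may be wider than it looks.** The Outcomes section speaks of each index, and the scale-group section calls men *indexes* before any consent. Read with the intention-to-treat statement, this could mean all selected SHIs, and a fuller plan may say so. But the Abstract and the Sample size section count index participants, whom the Interventions section defines by consent. As published, the text leads to consenters.
- **The direction is unknown.** A model trained to find key distributors could find men who consent more often, which would bias against it. This stands, and the claim is limited accordingly.

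Three stronger readings are tempting and are not supported.

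- A reader might infer that unblinded researchers influence who consents, because "Only researchers will know the details of the group assignments, and study participants and CBO staff are blinded". No section says who sends the notification or that its content differs by arm.
- A reader might infer that the outcome is conditioned on ordering. The procedure section keeps index participants who order nothing in the first round and invites them to the second, so they remain in the set; what removes a man is not consenting.
- A reader might infer that the Abstract and Interventions definitions produce materially different sets. Every survey, including the one at first order, carries an electronic consent form, so a direct orderer has normally consented. The difference may be one of wording only.

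**Conclusion.** The point holds in this form: as published, the primary denominator excludes identified SHIs who decline, which conflicts with the intention-to-treat statement and with an objective about SHIs identified by each method. The bias is zero if consent is equal and can run either way if it is not. In the illustration it is ±0.75 alters per index, three quarters of the planned difference of 1. A 10-point gap in consent (55% and 65%) raises the false-positive rate for the model from a nominal 2.5% to 16.6% under the simulation's assumptions.

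The documents neither show nor predict a consent imbalance, and every consent rate, yield and dispersion used here is assumed. The flaw lies in the choice of denominator; whether it does harm depends on data not yet seen.

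**What to change.** - Define the primary analysis set as all SHIs identified in each randomised arm, in the matched numbers already intended, analysed as randomised. Give a count of zero to those who decline, do not order or produce no verified alter. The zeros can be taken as real values: the Discussion says ordering is open only to identified SHIs, and results are captured on the platform.
- Use one definition of index participant, reconciling the Abstract with the Interventions section.
- Report consent and ordering rates by arm, and the per-index mean, as secondary results.
- Restate the effect sizes and power in the Sample size section on the new denominator. At 50% consent in both arms, the planned +1 per index becomes +0.5 per identified SHI.

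No new data collection is needed, and the Trial status section says analysis has not begun. The cost is a smaller mean difference per SHI and the modest loss of power worked out above, which in the case with 20% loss takes power slightly below the planned 0.80. In that case, restoring 0.80 would take about 2.80² × (5.24 + 5.99)/0.5² ≈ 353 evaluable identified SHIs per arm instead of 320.

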**Fig. 1 Fig1:**
[figure not shown]
Trial Flowchart

#### The scale group/ control group

SHIs among MSM participants assigned to the empiricalscale group (hereafter, scale group) will be determined using a 6-item scale. The same scale has been used by our team in a previous study [22, 23] to measure men’s sexual health influence, with a Cronbach alpha of 0.937. The scale consists of six questions that will assess each participants’ level of contribution in spreading HIV and sexually transmitted infections (STI) related information both online and offline in the past three months. The six questions include 1) how often they talked to others about HIV and STI; 2) how much information about HIV and STI they provided to others; 3) how many people they told about HIV and STI; 4) how likely they were to ask for more information about HIV and STI; 5) who communicated more information about HIV and STI: the participants or others within their social network; 6) how often they were to ask for advice about HIV and STI. Total response scores from answering the questions range from 0 to 24. Table 1 presents a detailed summary of responses to each question.

**Table 1 Tab1:** Summarized responses of each item in the conventional scale

Typical item	Responses Categories	Method of scaling
In the past 3 months, how often did you talk to others about HIV and STI (including both online and offline)?	Never, seldom, sometimes, often, always.	5-point Likert scale, from 0 (never) to 4 (always).
In the past 3 months, how much information about HIV and STI did you provide to others (including both online and offline)?	No information provided, provided with a little information, provided with some information, provided with much information, provided with massive information.	5-point Likert scale, from 0 (no information provided) to 4 (provided with massive information).
In the past 3 months, how many people did you tell about HIV and STI (including both online and offline)?	None, few people, some people, many people, a lot of people.	5-point Likert scale, from 0 (none), 4 (a lot of people).
In the past 3 months, how likely were you to be asked for more information about HIV and STI (including both online and offline)?	Very unlikely, unlikely, neutral, likely, very likely.	5-point Likert scale, from 0 (very unlikely) to 4 (very likely).
In the past 3 months, who communicated more information about HIV and STI: you or others within your social network (including both online and offline)?	All information was told by others, most of information was told by others, information that others told me about was as much as I told them, most of information was told by me, all information was told by me.	5-point Likert scale, from 0 (all information was told by others) to 4 (all information was told by me).
In the past 3 months, how often were you to be asked for advice about HIV and STI (including both online and offline)?	Never, seldom, sometimes, often, always.	5-point Likert scale, from 0 (never) to 4 (always).

We may eliminate some top-point indexes (by either 20% or 30%, or other percentages) depending on the actual situation we encounter during the data collection. Also, the machine learning identification of the number of SHIs will be according to the ranking descending from the highest total points. We will randomly select the required number of indexes amongst the eligible SHIs with the lowest scale total scale point if more indexes share the same total scale point score. For example, if we would like to cut off the top 35 indexes out of 100 participants, however, 27 indexes scored at least 20 points, and the subsequent 12 indexes (Rank No. 28 to Rank No. 39) score 19 points, then we will randomly select eight indexes among the 12 indexes (i.e., No. 28 to No. 39). That will ensure that the cut-off percentage of 35% predefined before the selection will remain equal to the same number of machine learning identification results.

#### The machine learning group/ intervention group

SHIs in the intervention group will be identified using an ensemble machine learning model, which we have trained using our previous SD-HIVST intervention trial data [24]. The data from our prior SD-HIVST intervention pilot served as our training and validation data set. And the identification of the results (i.e., classification accuracy) of our proposed machine learning model outperformed the conventional scales cut-off method [22].

We determined significant predictors according to machine learning algorithms, using training dataset and validation dataset in our previous modeling study [22]. Thus, we will include questions regarding these predictors in the baseline survey. We will collect data on these selected predictors and input them into our pre-trained ensemble machine learning model. Output results from the model will show who the SHIs are in the machine learning group. If some predictor variables have unavailable or missing data, our model will still work as we can regard those data as ‘NA’ data in modeling input for prediction. Also, we trained three ensemble machine learning models in our previous modeling study for identifying SHIs. The models could distinctly predict key distributors (SHIs who are likely to distribute at least two kits to alters), key promotors (SHIs who can promote HIV testing among the first-time tested alters), and key detectors (SHIs who can contribute to positive alters detection). However, we found that the model of key distributors is also capable of identifying most of key promotors. Therefore, in this study, we will utilize the model of key distributors for SHI identification in the machine learning group as our main outcomes focus on the ability of index on motivating alters and newly-tested alters.

